## Abstract

**Background:**

A nested process evaluation, within a randomised controlled trial, will explore relationships between program outcomes and quality of intervention implementation of the Lifestyle-Integrated Functional Exercise Program in older people with vision impairment. The Lifestyle-Integrated Functional Exercise Program is a home-based strength and balance program that has been shown to reduce falls in high risk populations. A pilot study showed positive trends in improvements in physical function in older people with vision impairment after participation in the program. The program will be delivered by Orientation and Mobility Specialists, who are experienced in working with people with vision impairment.

**Methods:**

The process evaluation has a mixed methods design. This includes quantitative (fidelity checklist score, number of completed sessions, survey data and a habit formation scale), as well as qualitative (open responses from program staff and semi-structured interviews with study participants) data. Process evaluation measures include program adherence (fidelity), complete delivery (dose delivered), participant receipt (dose received) and participant enactment. Using the Behaviour Change Wheel, a logic model was built to explain the intended inputs, outputs, outcomes and relationships to the behaviour change techniques in the Lifestyle-Integrated Functional Exercise Program in older people with vision impairment.

**Discussion:**

The findings of the process evaluation will inform the provision of fall prevention programs in older people with vision impairment by Orientation and Mobility Specialists. To date, there are no proven falls prevention programs which aim to improve physical function and reduce falls in older people with vision impairment. This process evaluation will contribute new knowledge about the implementation of a strength and balance program in this population.

**Trial registration:**

ACTRN12616001186448. Registered 29 August 2016.

**Electronic supplementary material:**

The online version of this article (10.1186/s12913-018-3304-6) contains supplementary material, which is available to authorized users.

## Background

Older people with vision impairment are eight times more likely to fall than their sighted peers [1]. With an ever increasing population of older people with vision impairment [2], it is crucial to carefully evaluate large scale fall prevention interventions that target this population. A 2012 Cochrane Review concluded that home and group-based exercise programs, along with home safety and medical management, reduce the rate and risk of falling in older people [3]. A recent systematic review by Sherrington et al. [4] identified that exercise as a single intervention can reduce falls by 21% in community dwelling older adults, particularly those interventions that include a high challenge to balance. Although programs which challenge strength and balance, such as the Otago Exercise Programme, have been found to reduce falls by up to 35% in the general population [5], one trial found no significant reduction in fall risk of participants with vision impairment [6].

The Lifestyle Integrated Function Exercise (LiFE) program [7] has been adapted for older people with vision impairment (v-LiFE) and evaluated in a pilot study. The v-LiFE program was delivered by Orientation and Mobility (O&M) Specialists, who have extensive experience delivering programs which increase independence and safety of those with vision impairment. A statistically significant reduction in fear of falling and improved late life function, as well as non-significant trends towards improvements in physical outcomes were reported, following participation in the program. Most participants were able to complete the program, and appreciated its benefits. It was concluded that O&M Specialists were well suited to delivering the v-LiFE program to this population. The pilot study did not have a control group or directly measure falls, but does provide support for a larger scale trial [8].

A larger scale single-blinded randomised controlled trial known as the PrevenTing Falls in a high risk, vision impaired population through specialist ORientation and Mobility services (PlaTFORM) commenced in 2017. A comprehensive protocol of the PlaTFORM study has been published elsewhere [9]. In brief, the aim of PlaTFORM is to investigate whether v-LiFE can prevent falls and increase physical function in older people with vision impairment, compared with usual care. Usual care refers to typical programs delivered by O&M Specialists to people with vision impairment. These programs focus on teaching people with vision impairment how to identify where they are and where they want to go (orientation), as well as how to move safely and efficiently from one place to another (mobility). Examples of a program could be orientation and mobility in the home, or catching public transport to work. As each program is specific to the goals of each person, they can vary dramatically in complexity, but are typically achieved within 6 months.

A process evaluation is particularly important in trials of complex interventions and is a common method in determining the factors which influence the level of success of an intervention [10]. The UK Medical Research Council (MRC) [10] recommend process evaluation protocols are published to ensure transparency in the development and implementation of interventions, as well as dissemination of results. This process evaluation protocol is designed to explore the development, implementation and efficacy of an intervention designed to improve physical function, and ultimately, reduce falls in older adults with vision impairment.

## Methods

In this paper, we outline the aims and corresponding methods for the PlaTFORM process evaluation. The overarching aim is to understand the relationship between program implementation and acceptability, and program outcomes [11]. More specifically, (1) to explore if the PlaTFORM trial was delivered as intended (i.e. idelity and dose delivered) and (2) to understand whether, how and why the intervention had an impact, through exploring participants’ perspectives and enactment of the intervention (i.e. participant receipt and participant enactment).

We aim to recruit 588 community dwelling people with vision impairment, aged 50 years or above. After baseline assessment, participants will be randomly assigned to the intervention or control group. The intervention group will receive the v-LiFE program plus usual care (an Orientation and Mobility program), while the control group will receive only usual care. This process evaluation will only include data from the intervention group.

### Program description

The v-LiFE program is designed to incorporate strength and balance activities into the everyday activities of older people with vision loss, living in the community, who are at high risk of falls. The intervention group will receive usual care as well the v-LiFE program over five weekly sessions, plus two booster visits and two phone calls within three months. If required, participants will receive up to two additional sessions. All sessions will be delivered in participants’ homes by O&M Specialists from Guide Dogs NSW/ACT. The control group will receive usual care.

The strength and balance activities will be catered to each participants’ physical function as they move through the program. As participants improve their strength and balance they will be encouraged to upgrade to more challenging exercises (i.e. reducing their base of support or increasing the weight lifted). O&M Specialists will be able to tailor their approach for each participant, which is in line with consensus that programs need to account for the individual context when delivering interventions [12]. Specially designed v-LiFE Participant manuals were produced for this population in audio, large print and electronic format.

### Implementation of v-LiFE

The implementation of the v-LiFE program will consist of three essential components [11]: training, intervention delivery and intervention enactment. Participants will also undergo a fourth component, assessment [11], at baseline and 12-months. These data will be collected as part of the trial outcomes for PlaTFORM and are described elsewhere [9].

#### The training component

More than 50 O&M Specialists from 10 offices, in six regions of NSW/ACT, will participate in two days of training. To assist in training and participation of those in regional areas, O&M Specialists will be able to take part in one of three possible training sessions (two will take place in Sydney NSW, and one in Northern NSW). The first day of training will consist of training in the delivery of the v-LiFE program and the second day will consist of training in research procedures. Each session will be facilitated by the same trainers (v-LiFE program: LC, JM).

#### The intervention delivery component

O&M Specialists will then deliver the v-LiFE program to older adults with vision impairment. This will be completed through (a) five weekly sessions, (b) two booster visits within three months, (c) two support calls after the visits are completed, and (d) if required, two additional sessions. Trainer and participant v-LiFE manuals have been designed for this population, which are to be closely followed in each session. To enhance self-efficacy, O&M Specialists are required to give positive reinforcement, encourage the use of self-monitoring tools and to assist in setting personal goals for short-term achievements.

#### The intervention enactment component

Participants will be required to incorporate the strength and balance activities, learnt during sessions, into their daily activities.

### Conceptualising v-LiFE with the behaviour change wheel

Michie et al. [13] developed the Behaviour Change Wheel (BCW), as a model for designing and evaluating interventions, as well as dissemination of results. The three domains of the BCW highlight the relationship of policy, intervention and the individual, which influence successful behaviour change. By participating in the v-LiFE program, participants will have to actively change their behaviour to incorporate the strength and balance activities into daily life. The BCW describes behaviour change through three *sources of behaviour* (inner wheel): capability (psychological, physical), opportunity (social, physical) and motivation (automatic, reflective). These behaviour changes will be facilitated by the O&M Specialists, which fall under *intervention functions* (middle wheel) of the BCW. Of the nine intervention functions, the components which are particularly relevant for our trial are: education, persuasion, coercion, training, incentivisation and enablement. Within the intervention functions are behaviour change techniques (BCTs), which are the ‘active ingredients’, designed to change behaviour. Guide Dogs NSW/ACT will support the O&M Specialists in their training of the v-LiFE program with participants. The BCW wheel includes seven *policy categories* (outer wheel), of which, service provision is considered particularly relevant to this study.

Table 1 shows specific measures that will be undertaken as part of the process evaluation and how they relate to the BCW model and BCTs.

**Table 1 Tab1:** Process evaluation procedures mapped to measures, outcomes and Behaviour Change Techniques

Component		Question	Method/Measure	Data Type	Outcomes	^a^Behaviour Change Techniques (Intervention Function)
**1.**	Program Adherence (Fidelity)	How well did the O&M Specialists deliver the v-LiFE program to participants?	• A trained observer will observe 1–2 participant sessions with each instructor using a checklist, while making comments (20% of all v-LiFE program participants).	Quantitative	Higher scores indicate well delivered v-LiFE programs	Feedback on behaviour (Education/Persuasion/Coercion); Credible source (Persuasion); Instruction on how to perform the behaviour (Training); Problem solving (Enablement)
				Qualitative	Analysis of observer’s comments using the BCW as a framework	
**2.**	Complete Delivery (Dose delivered)	To what extent were all of the intended components of the v-LiFE program delivered to participants?	• O&M Specialists to record each time they complete a session, booster session, additional sessions and/or phone calls.	Quantitative	Higher scores indicate participants received a higher program dose	Self-monitoring of behaviour (Education/Incentivisation); Monitoring of behaviour by others without evidence of feedback (Coercion); Prompt/cues (Education)
**3.**	Participant Receipt (Dose received)	To what extent were participants engaged/satisfied with the v-LiFE program?	• Semi-structured interview (30 participants).	Qualitative	Analysis of transcripts using the BCW as a framework	Information about health consequences, self-monitoring of behaviour (Education); Monitoring of behaviour by others without evidence of feedback (Coercion)
			• Short answer survey (all participants).	Quantitative	Higher scores on the AFRIS indicate higher engagement to v-LiFE	
**4.**	Participant Enactment	To what extent were the participants completing the prescribed activities?	• The Self-Report Habit Index (post-program)	Quantitative	Higher scores on the Index indicate stronger habit formation	Self-monitoring of behaviour (Education/Incentivisation/Coercion); Feedback on behaviour (Education/Incentivisation/Coercion); Monitoring of outcome of behaviour by others without evidence of feedback (Incentivisation/Coercion

^a^ Michie et al. [13], BCW: Behaviour Change Wheel. AFRIS: Attitudes to Falls-Related Interventions Scale

### Process measures

The process evaluation is a mixed methods design. This includes quantitative (fidelity checklists, number of completed sessions and survey data), as well as qualitative (semi-structured interviews) data collection. Process evaluation measures include program adherence (fidelity), complete delivery (dose delivered), participant receipt (dose received) and participant enactment.

#### Program adherence

Program adherence (fidelity) is a measure of what extent the intervention was developed and used as intended [11]. The theoretical underpinning of v-LiFE is habit retraining [14]. As there are more than 50 O&M Specialists delivering the program, it is important to assess whether all the participants are receiving equivalent training. O&M Specialists need to encourage the participants to incorporate the skills they learn through sessions into everyday activities. This self-efficacy is facilitated through: positive reinforcement from the instructor, self-monitoring and setting achievable short-term goals.

Program adherence will be measured through direct observation of participant sessions by an observer trained in the delivery of v-LiFE. Each instructor will be observed completing 1–2 sessions with participants, to cover approximately 20% of all v-LiFE program participants. A v-LiFE fidelity tool checklist (Additional file 1: Appendix 1) will be used in each observation to ensure consistency in assessment. The checklist is designed to assess whether sessions adhere to the program as designed and set out in the program manual, and the quality of delivery, including: content, key features, credibility, skill, language, verbal and active teaching strategies. Wherever possible, the observer will also provide feedback to the Instructor to improve service delivery.

#### Complete delivery

Complete delivery (dose delivered) is a measure of the number of intended v-LiFE sessions and phone calls provided to participants [11]. In order for complete delivery, O&M Specialists will be required to deliver 5 weekly sessions, 2 booster visits and 2 follow-up phone calls. O&M Specialists are also able to provide an additional 2 sessions if required by the participants. Program session data will be collected from the Guide Dogs Customer Relationship Manager (CRM) database. As with any O&M program and associated program sessions, O&M Specialists will be required to detail the name, date, travel time, travel distance, session objectives and session outcomes in Guide Dogs CRM database. This will be a record of sessions and phone calls and personnel involved.

#### Participant receipt

Participant receipt (dose received) is a measure of participant’s engagement and understanding of the program content of v-LiFE, as well as their satisfaction with the program [11]. Participant receipt will be measured through semi-structured interviews and survey questions (Additional file 2: Appendix 2) following program completion. Participants in the intervention arm will be invited to complete the semi-structured interview and survey questions over the phone by a researcher not involved in the delivery of v-LiFE. Both the semi-structured and survey questions have been adapted from the Attitude to Falls-Related Intervention Scale (AFRIS). Based on the Theory of Planned Behaviour, the AFRIS helps to identify why or why not participants have engaged in a fall prevention intervention, through analysing what is considered acceptable to a participant [15].

#### Participant enactment

Participant enactment is a measure of what extent the knowledge and skills gained from completing the v-LiFE program are applied to participants’ everyday life. The v-LiFE program requires participants to actively engage in activities and opportunities that incorporate strength and balance into their daily routines. Habit formation is considered a core component of enabling people to perform LiFE activities routinely [14]. Consequently, in the initial v-LiFE session, the O&M Specialist will work with the participant on identifying opportunities in their daily routines which are associated with particular situations which will prompt the participant to practise the strength and balance activities. Participant enactment will be measured through the Self-Report Habit Index [16]. Hackney et al. [16] designed the index to measure habit strength, without the need to measure behavioural frequency of an activity. Habit strength refers to the frequent and satisfactory pairing of specific cues and automatic responses. For example, the pairing of a daily activity (specific cue), such as brushing teeth, with a v-LiFE activity (automatic response), such as practicing a tandem stand. Following the completion of the v-LiFE training, participants will be asked to complete the Self-Report Habit Index with a research assistant. The participant will be asked to answer the index for (a) a v-LiFE activity they enjoy or did not find challenging to incorporate into daily life, and (b) a v-LiFE activity they did not enjoy or found challenging to incorporate into daily life (Additional file 3: Appendix 3).

### Data analysis

Descriptive statistics will be used to summarise baseline demographic, vision and functional characteristics of intervention participants. In line with the MRC [10], quantitative data will be analysed prior to knowledge of trial outcomes to reduce bias. The quantitative and qualitative analyses will build upon one another, to help explain findings [10], and test the proposed logic model (Fig. 1).

**Fig. 1 Fig1:**
[figure not shown]
Logic model for PlaTFORM and v-LiFE implementation evaluation. O&M, Orientation and Mobility; VI, Vision Impairment; SPPB, Short Physical Performance Battery; LLFDI, Late Life Function Disability Index; RR Statistic, Risk Ratio Statistic; AFRIS, Attitudes to Falls Related Intervention Scale

#### Sample size

The PlaTFORM study was powered to be able to compare fall rates between control and intervention arms of the main RCT and required a total of 588 participants (294 per group) to detect a 30% between-group difference in falls rate, with 90% power at the 5% level, allowing for a 15% drop-out [9]. Consequently, quantitative data from up to 294 participants will be available for the process evaluation. This sample size will be sufficient to quantify the variation in scores for program fidelity, dose delivered, dose received through the AFRIS scale and enactment through the habit formation index. For qualitative data, it is expected this sample size will enable thematic saturation.

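### The sample-size paragraph justifies fidelity and the qualitative work by up to 294 participants, but the design gives about 59 fidelity observations and 30 interviews, so both statements rest on the wrong n

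*Protocol article*

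**What the plan says.** The Sample size section starts from the main trial, which "required a total of 588 participants (294 per group) to detect a 30% between-group difference in falls rate". That calculation uses a 5% significance level, 90% power and an allowance of 15% for loss. From it the article concludes that up to 294 intervention participants will supply quantitative data for the process evaluation. It then states: "This sample size will be sufficient to quantify the variation in scores for program fidelity, dose delivered, dose received through the AFRIS scale"; the sentence goes on to include the habit index. The next sentence reads: "For qualitative data, it is expected this sample size will enable thematic saturation".

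Two other places set how many observations these components actually have:

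- Program adherence section: "Each instructor will be observed completing 1–2 sessions with participants, to cover approximately 20% of all v-LiFE program participants". Table 1 repeats the 20%. The same section says that more than 50 Orientation and Mobility (O&M) Specialists will deliver the program, and gives this as the reason to check that participants receive equivalent training.
- Table 1, participant receipt row: "Semi-structured interview (30 participants"). The short survey in the same row is for all participants.

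The Quantitative data section uses the fidelity score in two ways: descriptive statistics, and a ranked correlation matrix of the process measures.

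**The concern.** In the Sample size section the demonstrative can only point back to the sample just described, up to 294 participants. That is a fair ceiling for dose delivered, AFRIS and the habit index, which are sought from everyone in the intervention arm. It is not a ceiling that fidelity or the interviews could approach, because the design caps them well below it before any loss occurs.

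Fidelity is the first process measure listed, and its correlations with dose, receipt and enactment are part of how the logic model is to be tested. If the only sample size given for the evaluation is 294, a weak or null fidelity correlation may be read as a fairly precise result when its interval is more than twice as wide. Saturation is likewise attached to a number about ten times the number of people interviewed.

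**Working it through.** **Inputs.** Intervention arm 294 (588 / 2; Sample size section). Fidelity fraction about 20%, 1–2 sessions per instructor, more than 50 instructors (Program adherence section; Table 1). Interviews 30 (Table 1). Ranked correlations (Quantitative data section).

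**The plan's own figure.** 588 / 2 = 294 is correct. The 588 itself cannot be reproduced from the article, because the control fall rate, dispersion and follow-up are left to the main-trial protocol. Nothing below depends on it.

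**Observations available.**
- Fidelity by the 20% rule: 0.20 × 294 = 58.8, about 59.
- Fidelity by the 1–2 sessions rule with 50 instructors: 50 to 100 observations, or 50/294 = 17% to 100/294 = 34%. The 20% figure lies near the lower end.
- Interviews: 30/294 = 10%.

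**Precision.** Three standard calculations, treating observations as independent:
- 95% limits on an SD, as multiples of the estimate: √[(n−1)/χ²(0.975, n−1)] to √[(n−1)/χ²(0.025, n−1)]. At n = 59: √(58/80.94) = 0.85 and √(58/38.84) = 1.22.
- Smallest rank correlation detectable with 80% power, two-sided 5%: tanh[(1.960 + 0.842) × √(1.06/(n−3))], where 1.06 is the usual variance factor for ranks. At n = 59: tanh(2.802 × √(1.06/56)) = tanh(0.385) = 0.37.
- 95% interval for an observed rank correlation of 0.30: tanh[0.3095 ± 1.96 × √(1.06/(n−3))]. At n = 59: tanh(0.3095 ± 0.2697) = 0.04 to 0.52.

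| n | 95% limits on SD | Detectable correlation | 95% CI for 0.30 |
|---|---|---|---|
| 294 (as stated) | −7% / +9% | 0.17 | 0.19 to 0.40 |
| 100 (two sessions × 50 instructors) | −12% / +16% | 0.28 | 0.10 to 0.47 |
| 59 (20% rule) | −15% / +22% | 0.37 | 0.04 to 0.52 |
| 50 (one session × 50 instructors) | −16% / +25% | 0.40 | 0.02 to 0.54 |

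At 59 the interval for 0.30 is 0.482 wide against 0.215 at 294, a ratio of about 2.25.

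**Instructor structure.** 59/50 is about 1.2 observations per instructor. If all 50 are seen, 59 − 50 = 9 degrees of freedom remain within instructor, and the 95% limits on the session-to-session SD are ×0.69 to ×1.83. With 55 instructors only 4 remain (×0.60 to ×2.87). The overall spread of scores can be estimated; its split between instructors and sessions hardly can. Nesting does little to the effective sample size for the mean: with 9 instructors seen twice and 41 once, the design effect is 1 + (77/59 − 1) × ICC. For an assumed ICC of 0.1 to 0.8 this is 1.03 to 1.24, an effective n of 57 to 47.

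**Scale.** The Quantitative data section scores the initial session from 39 to 117 and later sessions from 29 to 87. Raw totals from the two checklists are not on one scale, so the directly comparable observations are fewer than 59 unless the scores are standardised.

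**The case against.** The strongest reply is that the article claims only enough data to quantify variation, and that 59 observations do so: an SD known to −15%/+22% is a usable description. No precision target, power or saturation criterion is stated that 59 or 30 would fail. The words up to mark 294 as a ceiling, and the 20% and the 30 interviews are stated openly. Saturation is only expected, and the abstract and Table 1 add open responses from program staff and observers' comments to the interviews.

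Most of this stands, and it limits the point. A reader might infer that the claimed sufficiency is wrong, or that 30 interviews are too few; the article supports neither. What the reply does not meet is that the reason offered is a sample of up to 294, and neither component has that sample.

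Three further inferences should also be resisted.
- That AFRIS and the habit index will have about 250 respondents (294 × 0.85). The 15% drop-out belongs to the main trial's fall-rate calculation; these measures follow program completion, and no loss figure is given for them.
- That correlations will treat all of an instructor's participants as independent. Nothing in the article says an observed score will be carried over to participants who were not observed.
- That nesting greatly reduces the fidelity sample. At about 1.2 observations per instructor it does not.

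**Conclusion.** The point holds as a mismatch between the stated justification and the design. The Sample size section credits fidelity with about five times the observations planned (294/59) and the interviews with about ten times (294/30). Both statements are therefore unsupported as argued. Whether about 59 observations and 30 interviews are adequate remains open, because no criterion is given.

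The practical size lies in the correlations: at about 59 pairs, only rank correlations of about 0.37 or more would be detected with 80% power. The stated reason for measuring fidelity, whether training is equivalent across instructors, is only weakly addressed at about 1.2 observations each.

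These figures assume the approximate 20% is met and, for the within-instructor calculation, exactly 50 instructors. Observing every instructor twice would give 100 observations, a detectable correlation of about 0.28 if they were independent, and far better separation of instructor from session. That is still well short of what 294 implies. The main trial's power and primary comparison are unaffected.

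**What to change.** In the Sample size section, replace the single figure by n for each component:

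- dose delivered, AFRIS and habit index: up to 294, less any loss;
- fidelity: about 59 observations on more than 50 instructors;
- interviews: 30, with observers' comments and staff open responses as additional qualitative material.

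Give the resulting precision for the fidelity score and its correlations, and base the sufficiency and saturation statements on these numbers. In the report, show each fidelity correlation with its own n and confidence interval, so that a null result is not taken to come from 294 participants.

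The cost is a few sentences and less favourable stated figures. No extra participants or observers are needed.
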